### **3. Trial design**

We will use a mixed methods design for this study, containing both a quantitative and a qualitative component. The quantitative component is presented first and the qualitative component follows. An open-label randomized controlled trial will be used for this study. Patients will be randomized to one of 3 groups: a RM, a SM intervention group and a SC group (41 patients per group).

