### **4. Methods**

#### **a. Study Setting**

The study will be conducted at Markham Stouffville Hospital (MSH) with most patients being recruited from the Outpatient COPD Clinic (Respiratory Health-COPD Clinic). Recruitment will be coordinated internally by the clinical project specialist, who is also a respiratory therapist. Some patients will also be identified through inpatient admission records and the Health for All Family Health Team (FHT) by their family doctors who have clients that are living in the community with diagnosed COPD. Additional patients will be recruited by respirologists. These respirologists practice at the Outpatient COPD clinic, but also have separate private practices in Markham. Finally, patients will be recruited from the Outpatient COPD Exercise Rehabilitation Program that is run at the Cornell Community Centre in collaboration with MSH. These patients will be approached by an MSH respiratory therapist who coordinates the rehabilitation program. We have already established a research collaboration with the hospital during the design phase of this project that informed our methods and recruitment practices. Access to potential patients will be determined locally, in-house at MSH by the clinical project specialist, who is also a respiratory therapist. All data collection will be done internally at MSH. All initial contact will be done internally to the site from where the patient is originating (e.g. Outpatient COPD Clinic, COPD rehabilitation program, Family Health Team (FHT), or a respirologists' private practice). For sites that are outside MSH, patients will be provided with the brochure for the study and will be asked for permission to be contacted by the clinical project specialist.

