#### d. Intervention

Patients will be randomized to either SM, RM group or SC group (41 patients per group). Patients in the SM and RM group will receive the Cloud DX kit at the start of the trial and will continue using it for 6 months. Patients in the SC group will be given the opportunity to receive the kit at the end of the trial and use it for free for 6 months (see Figure 1). All patients will complete 3 assessments: at baseline, 3 months and 6 months on a series of questionnaires (see Outcome section for a list and description). They will also complete a demographic questionnaire at the initial visit (Appendix 13). The clinical project specialist at MSH will be responsible for collecting all data at each visit. The initial visit is expected to take 2 hours, allowing for obtaining consent, an introduction of the kit, and survey completion. Subsequent visits are expected to take about 1 hour to complete, as only surveys will be filled out. Visit 2 and 3 will be done in-person or remotely as surveys will be completed through REDCap and patients will have the option to complete them online from their home or over the phone. The clinical project specialist will make contact with the patient via telephone to remind them of the survey deadline. If patients prefer to come in person, they will be provided with that option. If the patient prefers to conduct the survey over the phone, they will be transferred over to the research team at WCH with a script (Appendix 20). Once the patient verbally agrees, the clinical project specialist at MSH will call one of the Research Assistants at WCH to provide the patient name, telephone number, and email address (if applicable). If the Research Assistant does not pick up, a voice message will be left on the Research Assistant's password protected mailbox. The Research Assistant then documents patient information in a password protected Excel document in the WCH internal drive. The Research Assistant will then contact the patient to conduct the survey as well as email the patient for any follow-up requests from the phone call, ie. to resend the REDCap survey link.

Patients in the SM and RM group will also be contacted by the clinical project specialist 2 weeks after receiving their kit to review whether their thresholds have been set properly. If a revision of the thresholds is needed this will be done with the respirologist's approval.

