##### ii. Secondary Outcomes

- Quality of Life and Respiratory symptoms will be assessed with the *St. George's Respiratory Questionnaire (SGRQ)* (Jones, Quirk, & Baveystock, 1991) (Appendix 10).

The St. George's Respiratory Questionnaire (SGRQ) is an index designed to measure and quantify health-related health status in patients with chronic airflow limitation. It has been shown to correlate well with established measures of symptom level, disease activity and disability. The first part ("Symptoms") evaluates symptomatology, including frequency of cough, sputum production, wheeze, breathlessness and the duration and frequency of attacks of breathlessness or wheeze. The second part has two components: "Activity" and "Impacts". The "Activity" section addresses activities that cause breathlessness or are limited because of breathlessness. The "Impacts" section covers a range of factors including influence on employment, being in control of health, panic, stigmatization, the need for medication, side effects of prescribed therapies, expectations for health and disturbances of daily life.

- Bristol COPD Knowledge Questionnaire (White, Walker, Roberts, Kalisky, & White, 2006) (Appendix 18) is a measurement of COPD patients' disease knowledge level. It consists of 13 subscales, each of which assesses a topic of COPD knowledge: (1) epidemiology, (2) aetiology, (3) symptom, (4) breathlessness, (5) phlegm, (6) infections, (7) exercise, (8) smoking, (9) vaccination, (10) inhaled bronchodilators, (11) antibiotics, (12) oral steroids, and (13) inhaled steroids. This test has been used in the past to assess patients' knowledge of COPD (Choi, Chung, & Han, 2014; Zhang et al., 2014).
- The COPD Assessment Test (Jones et al., 2009) (Appendix 7)
- MRC Breathlessness Scale (Stenton, 2008) (Appendix 8)
- Patients will also be asked to self-report at baseline, 3m and 6m the following measures for the past 3 months: the number of ED presentations, number of admissions to a hospital, the length of stay for all admissions (in days), number of exacerbations (episodes in which antibiotics or steroids were prescribed or hospital/clinic visit due to a respiratory issue), number of visits to family doctor, number of nurse contacts, self-reported use of medication, self-reported smoking cessation (Appendix 13)
- Number of contacts/calls to the outpatient clinic and deaths will also be kept track of by the clinical project specialist at MSH

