## **Data collection, management, and statistical analysis**

All quantitative continuous data will be analysed by conducting a between-group repeated-measures ANOVA analyses comparing the scores at baseline, 3m and 6m follow-up assessments of each group. We will also run within-group comparisons, examining differences in performance between each assessment at baseline, 3m and 6m follow-up. All analysis will be run by a statistician at WIHV.

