### **Study Significance**

The use of technology has the potential to provide clinical marker feedback to the patient and the clinical care provider (RM group), resulting in better disease control and better self-management skills and quality of life. Both programs have the potential to result in fewer face-to-face visits (outpatient and inpatient admissions), but the RM group may be more effective in that regard due to its ability to directly communicate with patients. The goal is to empower patients and improve their self-management skills leading to faster resolution of their health concerns resulting in fewer complications that may lead to outpatient and inpatient visits. This will increase institutional capacity to offer extended healthcare services to more patients.

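### Length of stay is not defined for patients without an admission, and the repeated-measures ANOVA set for continuous data suits neither reading of it

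*Protocol*

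**What the plan says.** Protocol section 4.e.ii (Secondary Outcomes) introduces a set of health-care use items: "Patients will also be asked to self-report at baseline, 3m and 6m the following measures for the past 3 months". The set includes "number of admissions to a hospital" and, as a separate item, "the length of stay for all admissions (in days". Section 4.d applies the visit schedule to everyone: "All patients will complete 3 assessments: at baseline, 3 months and 6 months on a series of questionnaires".

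The section on data collection, management and statistical analysis then fixes the method: "All quantitative continuous data will be analysed by conducting a between-group repeated-measures ANOVA analyses comparing the scores at baseline, 3m and 6m". It makes no exception for the health-care use items.

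The Study Significance section states the hoped-for effect on admissions: "Both programs have the potential to result in fewer face-to-face visits (outpatient and inpatient admissions".

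The text leaves two things open: whether the item is summed over a patient's admissions or expressed per admission, and what is recorded for a patient with none.

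**The concern.** The two readings are different outcomes.

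- **Per admission.** The value exists only for patients who were admitted in the window. Admission happens after randomisation, and the programmes are meant to reduce it. Comparing the admitted in one arm with the admitted in another is then no longer a randomised comparison. If mainly short stays are avoided, the mean among those left goes up, and a programme that saves hospital days looks harmful.
- **Total days.** Everyone who completes the visit has a value, but many values will be zero and the rest skewed to the right.

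The Background cites shorter stays as a benefit of remote monitoring, so this result will be read with interest. If the definition is still open when the data are seen, the choice lies between two summaries that can point in opposite directions.

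**Working it through.** **Inputs.** From the protocol: 41 patients per arm and 123 in all (section 3), and three visits, each with a 3-month recall. The protocol gives no figure for length of stay and no admission rate, so there is no stated result to reproduce. The admission share per window, p, is an assumption and is shown as a range.

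**1. Per-admission reading: who has a value?** In one window 41 × p patients per arm have a stay. With independent windows, N × p³ have a stay in all three.

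| p | with a stay in one window, per arm | in all three, per arm | in all three, of 123 |
|---|---|---|---|
| 5% | 2.1 | 0.01 | 0.02 |
| 10% | 4.1 | 0.04 | 0.12 |
| 20% | 8.2 | 0.33 | 0.98 |
| 30% | 12.3 | 1.1 | 3.3 |
| 50% | 20.5 | 5.1 | 15.4 |

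At p = 25% the last column is 123 × 0.25³ = 1.9. Clustering of admissions within patients would raise the last two columns.

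**2. Per-admission reading: which direction?** Assume that standard care has 0.15 short admissions (2 days) and 0.15 long admissions (8 days) per patient over 6 months.

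- Standard care: total 0.15 × 2 + 0.15 × 8 = 1.50 days per patient; per admission 1.50 / 0.30 = 5.0 days.
- Programme halves short stays only: total 0.075 × 2 + 0.15 × 8 = 1.35; per admission 1.35 / 0.225 = 6.0.
- Programme halves both: total 0.75; per admission 0.75 / 0.15 = 5.0.
- Programme halves long stays only: total 0.15 × 2 + 0.075 × 8 = 0.90; per admission 0.90 / 0.225 = 4.0.

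Simulating the short-stays-only case with Poisson admissions and 41 per arm, stay per admission is longer in the programme arm in about 76% of trials, although its expected total is lower.

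**3. Total-days reading: share of zeros.** At each visit the share is 1 − p: 95% at p = 5%, 75% at 25%, 50% at 50%. With the rates in step 2, standard care has exp(−0.15) = 86% zeros in a 3-month window and exp(−0.30) = 74% over 6 months.

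**4. Total-days reading: efficiency of the ANOVA.** Take equal variance σ² at each visit, a common correlation ρ between visits, and an effect of the same size at 3 and 6 months. The group-by-time test then rests on the follow-up mean minus baseline, with variance σ²[(1 + ρ)/2 + 1 − 2ρ] = 1.5σ²(1 − ρ). The follow-up mean adjusted for baseline has variance σ²[(1 + ρ)/2 − ρ²].

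- ρ = 0: 1.5 against 0.5, ratio 3.0
- ρ = 0.3: 1.05 against 0.56, ratio 1.9
- ρ = 0.5: 0.75 against 0.50, ratio 1.5
- ρ = 0.85 (the protocol's value for its questionnaire scores): 0.225 against 0.2025, ratio 1.1

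Sparse admission data probably have a low ρ. For two arms and three visits, the interaction also spends 2 degrees of freedom where the adjusted comparison spends 1.

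Simulations under two assumed sets of admission rates gave power 0.21 for a plain linear ANCOVA on the 0-6 month total against 0.08 for the group-by-time test, and 0.39 against 0.13, with type I error near 5%. The algebra agrees at ρ = 0. Power 0.21 on 1 degree of freedom is a noncentrality of 1.32, and a third of that (0.44) on 2 degrees of freedom gives 0.08. Likewise 0.39 is 2.82, and 0.94 on 2 degrees of freedom gives 0.13.

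**The case against.** The strongest reply is that one answer per patient per window, covering all admissions, most naturally means total inpatient days. It follows a count of admissions for which 0 is a valid answer, and no admissions then means 0 days. The protocol nowhere plans a mean among the admitted. The questionnaire and the chart review tool (Appendices 13 and 22) are not shown and may settle the scoring, and a zero-or-missing rule is often left to an analysis plan. The direction problem also depends on which stays are prevented: it vanishes when short and long stays are halved alike, and reverses when only long ones are.

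Much of this stands. A reader might infer that the outcome exists only for admitted patients and that most patients will have no value. The documents do not support that. The first is one of two readings. The second also needs an admission share below 50%, and no share is given. Recruitment is mainly outpatient ("most patients being recruited from the Outpatient COPD Clinic"), but some patients come from inpatient records, so the baseline share could be higher than in the later windows. The number of admissions is also a separate outcome, so prevented admissions would be visible beside any change in stay.

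The reply does not remove the point. The protocol itself fixes the ANOVA, and that method is a poor match even on the more favourable total-days reading.

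**Conclusion.** The concern holds as one of definition and method. The outcome has two readings, the protocol does not choose between them, and the stated ANOVA suits neither.

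Per admission, it would keep almost nobody or compare groups selected after randomisation, and could mislead on direction if mainly short stays are avoided. The move from 5.0 to 6.0 days shows the mechanism and does not predict its size. As total days, the data are likely to be mostly zero. The group-by-time contrast has up to three times the variance of the baseline-adjusted follow-up mean, and the ratio shrinks towards 1 as correlation between visits rises. The simulated power advantage of about 2.7 to 3 times applies at near-zero correlation and under assumed rates.

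This is minor. Length of stay is one secondary item, and neither the primary outcome nor the sample size depends on it.

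**What to change.** In section 4.e.ii, define the item as total days in hospital per randomised patient over months 0-6, the sum of the 3-month and 6-month reports, counted as 0 when there was no admission.

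In the statistical analysis section, exempt this outcome from the repeated-measures ANOVA. Compare arms with a method for skewed, zero-heavy data, for example negative binomial regression or a bootstrap of the mean difference, with the baseline 3-month total as covariate. State how a missing 3-month or 6-month report is handled, and how patients who die before reporting are counted. Report stay per admission descriptively only.

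The cost is one sentence in the outcome list and a few lines of analysis text. No new data are needed, provided that the form records days for all admissions as the outcome list says. The drawback is a wide interval, because total days will be skewed with many zeros at 41 per arm.

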## **Data collection, management, and statistical analysis**

All quantitative continuous data will be analysed by conducting a between-group repeated-measures ANOVA analyses comparing the scores at baseline, 3m and 6m follow-up assessments of each group. We will also run within-group comparisons, examining differences in performance between each assessment at baseline, 3m and 6m follow-up. All analysis will be run by a statistician at WIHV.

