#### **c. Recruitment**

Recruitment will be on-going until 123 patients have been recruited for the intervention phase (see sample size justification in Section 6.b). Patients will be approached by the clinical staff (respirologist or respiratory therapist-RT) who will introduce the technology to them and provide them with brief information about the trial with a brochure (Appendix 19) and request permission to pass the patient's information to the clinical project specialist at MSH. At this time the consent

form will also be given to give the patients enough time to consider participation. The clinical project specialist will later call the participants to further inquire about their interest in participating and to provide further details about the project. At this time they will also confirm the patient has a copy of the consent form and if they don't have the clinical project specialist will email it to the patient. The patients who are still interested in the project will be scheduled for their baseline evaluation, at which time informed consent will be signed (Appendix 1) and the Cloud DX kit will be provided to them. Patients can split that session into two, if they feel it is too much for one visit. There will also be a recruitment video that will be uploaded on YouTube. The clinical project specialist will email the link with the brochure to interested patients. The clinical project specialist will also be showing the video on a tablet to patients in the Outpatient COPD Exercise Rehabilitation Program. The Inpatient RT will show the video on a tablet to patients with COPD prior to their discharge from hospitalization.

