All physiological and symptom recordings taken by the patients will be transmitted to a secure Web site where they can be accessed by a pre-determined set of the patient's clinical care providers. The clinical project specialist at MSH will monitor each patient's recordings once a week and receive notifications when a patient's readings exceed the specific thresholds. The employee will screen any notifications or messages received once a day Mon-Fri. Each patient will have a personalized threshold level for their vitals that will be based on a threshold predetermined by the respirologist. The clinical project specialist monitoring the data for the RM group can access the data by looking at the Clinician Dashboard in this central web portal, accessible on any PC, Mac or mobile device. By monitoring blood pressure, pulse oxygen, temperature and body weight and using smart surveys, clinicians at MSH will have a better idea of the level of control each patient has over their COPD; which patients need the most help adjusting to their COPD management plan at home; and which COPD patients need to be seen in a community setting, maximizing scarce resources. Patients in the RM and SM groups will be instructed to refer to their action plan with each reading and follow the flow chart based on their symptoms and readings. The data of the patients in the RM group will also be screened at the clinic once a week, even if no notifications have been sent. Patients will be informed that their data will not be screened constantly and if they feel unwell, they should contact their clinical provider as they would do normally or go to the emergency room if they feel they need to see a doctor immediately or if the clinic is closed. Participants who have not entered data for a week will also be contacted by the clinical project specialist to inquire whether there is still interest in participation.

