### **f. Sample Size**

One self-management study (Walters et al., 2013) examined the effects of a telephone self-management program in COPD patients and used both the PIH scale and SGRQ. The effect size of the change over a 6m between the control and the intervention group was 0.42 for the PIH and -0.27 for the SQHQ. Assuming an  $\alpha=0.05$ , and correlation between repeated measures of 0.85, a total sample of 82 for a comparison between one of the intervention groups and the standard care group at baseline and 6m (41 patients per group) will produce power of 0.97 for PHI and 0.71 for the SGHQ. It is not clear whether we'd see any changes at 3m, but we are confident that we'd detect some effects at 6m.

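### The three-visit repeated-measures ANOVA would, in its classical form, drop patients who miss one survey, while 41 per arm is both the recruitment target and the analysed number behind the stated power

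*Protocol*

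**What the plan says.** **Analysis.** The section on data collection, management and statistical analysis says: "All quantitative continuous data will be analysed by conducting a between-group repeated-measures ANOVA analyses". The model takes in all three visits (baseline, 3 and 6 months). The section makes no exception for the primary outcome (PIH). It names no mixed model, imputation or other way to use incomplete patients.

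**Size.** Section c says: "Recruitment will be on-going until 123 patients have been recruited for the intervention phase". Section d says: "Patients will be randomized to either SM, RM group or SC group (41 patients per group"). Section 3 gives the same 41 per arm.

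**Power.** Section f takes effect sizes of "0.42 for the PIH and -0.27 for the SQHQ", alpha 0.05 and a correlation of 0.85. It states that one intervention arm against "the standard care group at baseline and 6m (41 patients per group) will produce power of 0.97 for PHI and 0.71 for the SGHQ". The same section doubts that any change will be visible at 3 months.

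**Loss the protocol itself foresees.**
- Under The Cloud DX Kit: "Participants who have not entered data for a week will also be contacted by the clinical project specialist", to ask whether they still wish to take part.
- The Risks section lets patients stop.
- The secondary outcomes include tracking of deaths.

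No drop-out rate is given, overall or by arm.

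**The concern.** Three statements fit together badly. The analysis uses three visits, the power uses two, and recruitment stops at the number the power needs to have analysed. A classical repeated-measures ANOVA works on complete rows. It therefore makes a patient's 6-month result depend on the 3-month survey, the visit from which the protocol expects least.

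Two things are at stake. One is precision, because 6-month scores that were collected would go unused and the stated power would not be reached. The other is selection, because an analysis of completers compares the arms as randomised only if completing is unrelated to outcome. The intervention arms record daily and can be contacted after a silent week. The standard-care arm has no kit during the trial. Completion could therefore differ between arms.

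**Working it through.** **1. Reproduce the stated power.** Inputs from section f: n = 41 per arm, d = 0.42 and 0.27, r = 0.85, alpha = 0.05. I assume d is in units of the SD at a single visit.

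- SD of change = √(2(1 − 0.85)) = √0.30 = 0.548.
- Non-centrality = (d / 0.548) × √(n/2). For n = 41 this is 3.47 (PIH) and 2.23 (SGRQ).
- One-sided, normal: Φ(3.47 − 1.645) = 0.966 and Φ(2.23 − 1.645) = 0.721. With the t distribution: 0.964 and 0.715.
- Two-sided, t: 0.929 and 0.597.

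The protocol's 0.97 and 0.71 are met to within about 0.01 by the one-sided change-score test. No other variant tried gives both:

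- two-sided change score: see above;
- baseline-adjusted, normal: 0.975/0.750 one-sided and 0.950/0.641 two-sided;
- effect size taken as already standardised for change, normal, one-sided: 0.60/0.34;
- within-between interaction F test: above 0.99 for both.

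The match uses all 41 per arm, so the stated power contains no loss. The protocol does not state sidedness, so both are shown below.

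**2. Patients kept.** Assume 10% miss 3 months and 10% miss 6 months, independently.

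- All three scores: 0.9 × 0.9 = 0.81; 41 × 0.81 = 33.2, about 33 per arm.
- Baseline and 6 months: 41 × 0.9 = 36.9, about 37 per arm.

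**3. Power on the same change-score test (t distribution).**

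| n per arm | PIH one-sided | PIH two-sided | SGRQ one-sided | SGRQ two-sided |
|---|---|---|---|---|
| 41 (no loss) | 0.964 | 0.929 | 0.715 | 0.597 |
| 37 (all with 6-month data) | 0.948 | 0.902 | 0.676 | 0.553 |
| 33 (complete on three visits) | 0.925 | 0.866 | 0.632 | 0.505 |
| 28 (30% loss) | 0.883 | 0.805 | 0.570 | 0.441 |

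Only n changes between rows, so the step from 33 to 37 is the effect of retention alone.

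**4. Selection, as an illustration.** Assume no true effect, unit variances and a correlation of 0.85 between every pair of visits. A fraction q of one intervention arm leaves, namely those with the lowest 3-month score given baseline. Nobody leaves standard care.

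- Covariance of the 3-month residual with 6-month change = r − r² = 0.85 − 0.7225 = 0.1275.
- SD of that residual = √(1 − 0.7225) = 0.527.
- Bias = (0.1275 / 0.527) × φ(z_q) / (1 − q) = 0.242 × φ(z_q) / (1 − q), where z_q is the q-quantile of the standard normal.

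| Loss in the intervention arm | φ(z_q)/(1 − q) | Bias in 6-month change | Type I error (simulated, two-sided 0.05) |
|---|---|---|---|
| 5% | 0.109 | +0.03 SD | about 5.5% |
| 10% | 0.195 | +0.05 SD | about 7% |
| 20% | 0.350 | +0.08 SD | about 10% |

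The sign is for a scale on which higher is better.

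**The case against.** **The exclusion is inferred.** A reader might take the protocol to say that incomplete patients are excluded. It does not. The exclusion follows from the classical form of the named method, and a statistical analysis plan that is not shown could fit a likelihood-based model. This stands as a limit on the claim. It does not remove the point, because the protocol does fix a method, and a plan that departed from it would leave the protocol text to be corrected.

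**Differential drop-out is not established.** A reader might infer that the randomised comparison is broken, with persistent technology users set against nearly all controls. The documents do not support that. They give no attrition figures. The contact after a silent week could retain patients as easily as lose them. Stopping daily entries is not the same as missing a questionnaire. Section d has every patient complete three assessments, whatever the kit use, with follow-up online, by phone or in person and telephone reminders. Selection is therefore a risk under assumed loss.

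**Power for the primary outcome is not in serious danger.** It stays above 0.80 even at 30% loss on either sidedness. A larger gain, to 0.923 (PIH) and 0.585 (SGRQ) two-sided at 37 per arm, is tempting to quote, but part of it comes from baseline adjustment and not from keeping patients.

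**The bias scenario is adverse by construction.** It removes the worst-scoring patients from one arm only. A mixed model removes that bias only if drop-out depends on observed scores. If patients leave because of an unrecorded 6-month state, it need not.

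**Conclusion.** The point holds as a choice of method that can be improved at almost no cost. In its classical form, the stated ANOVA would discard patients who have both scores on which the trial is powered. The stated power assumes that all 41 per arm are analysed, although the protocol foresees some loss.

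With 10% missing each follow-up independently, four patients per arm with 6-month data would go unused (37 − 33). That costs about 0.04 of two-sided power for PIH and 0.05 for SGRQ (about 0.02 and 0.04 one-sided). For PIH this is modest, and the possible selection of completers matters more. SGRQ starts at only 0.71 and has no reserve.

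The bias of +0.03 to +0.08 SD illustrates one adverse pattern of loss and is not a forecast. All of these sizes rest on assumed loss rates.

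**What to change.** - **Analysis section.** Replace the repeated-measures ANOVA with a linear mixed model fitted by maximum likelihood to all randomised patients as allocated, using every available score. Name the 6-month group contrast as the primary comparison.
- **Section f.** Restate the power for the number expected to have 6-month data, giving the assumed loss and the sidedness. At 10% loss (37 per arm, change-score test) it would read about 0.95 for PIH and 0.68 for SGRQ one-sided, or 0.90 and 0.55 two-sided.
- **Minor clarification.** Confirm that patients who stop using the kit still receive the 3- and 6-month questionnaires. Section d already implies this.

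The cost is wording in two sections and one added sentence. No extra patients or visits are needed.

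### No term of the planned repeated-measures ANOVA isolates the 6-month comparison with standard care on which the trial was sized

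*Protocol*

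**What the plan says.** The section on data collection, management and statistical analysis gives one between-group method for all continuous outcomes: "between-group repeated-measures ANOVA analyses comparing the scores at baseline, 3m and 6m follow-up assessments of each group". Baseline enters as a response level, not as a covariate. The section does not say which model term is the treatment test, which visit is primary, or which arms are contrasted. The only other analysis is within arms: "We will also run within-group comparisons, examining differences in performance between each assessment at baseline, 3m and 6m follow-up".

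The Sample Size section (4.f) starts from an earlier telephone self-management trial: "The effect size of the change over a 6m between the control and the intervention group was 0.42 for the PIH", and minus "0.27 for the SQHQ" (the SGRQ). It assumes alpha 0.05 and a "correlation between repeated measures of 0.85". The sized comparison is "a total sample of 82 for a comparison between one of the intervention groups and the standard care group at baseline and 6m", 41 per group, with stated power 0.97 for PIH and 0.71 for SGRQ. On timing it says: "It is not clear whether we'd see any changes at 3m, but we are confident that we'd detect some effects at 6m".

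Section 2 (Research Objectives) sets each programme, SM and RM, against standard care.

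**The concern.** The trial is sized on a contrast of two arms and two visits. It is to be analysed by an ANOVA over three visits and, as far as the wording shows, three groups. Such an ANOVA offers two candidate treatment tests, and neither is the 6-month effect of a programme against standard care.

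- The group main effect averages over visits. It includes baseline, where randomisation makes the expected difference zero, and 3 months, where the sponsor doubts there is one.
- The group-by-time term asks whether the arms' profiles differ in any way over the three visits.

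The first could miss a real 6-month effect. The second could be significant because of a different visit or a different arm. With the term left open, the choice could also be made after the data are seen. The within-group comparisons do not close the gap, because they do not use the randomised comparison.

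**Working it through.** **Inputs.** From the protocol: n = 41 per arm, alpha 0.05, ρ = 0.85, effects 0.42 (PIH) and 0.27 (SGRQ, absolute value). Assumed here: effects in units of the score SD (the protocol does not give the standardiser), zero baseline difference, compound symmetry, no dropout, two-sided tests unless stated. The 3-month effect is unknown, so it is set to none, half and all of the 6-month effect.

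**1. The stated power.** Two routes come within rounding or close to it.

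- Between-subjects F test, 2 groups and m = 2 visits, with 0.42 and 0.27 entered as Cohen's f: λ = f²·N·m/(1+(m−1)ρ), df 1 and 80. PIH: 0.42² × 82 × 2/1.85 = 15.6, power 0.974. SGRQ: 0.27² × 82 × 2/1.85 = 6.5, power 0.709. Both stated figures are matched to two decimals.
- One-sided t test on change, SD of change √(2(1−0.85)) = 0.548: 0.964 and 0.715.

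The two-sided change test gives 0.929 and 0.597. Two-sided ANCOVA gives 0.946 and 0.630. Neither reproduces the stated pair.

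**2. Group main effect over three visits.** Let D be the average of the three visit differences. For two arms, λ = n·m·(D²/2)/(1+(m−1)ρ). With no 3-month effect, D = 0.42/3 = 0.14 and λ = 41 × 3 × 0.0098/2.70 = 0.45.

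**3. Group-by-time term.** For two arms, λ = n·Σ(D_t − D)²/2/(1−ρ), where D_t is the difference at visit t. With no 3-month effect, the sum is 0.14² + 0.14² + 0.28² = 0.1176 and λ = 41 × 0.0588/0.15 = 16.07.

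PIH power, two arms (three-arm omnibus in brackets):

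| 3-month effect | D | Main effect | Group-by-time |
|---|---|---|---|
| none | 0.14 | 0.10 (0.10) | 0.95 (0.97) |
| half | 0.21 | 0.17 (0.16) | 0.88 (0.91) |
| full | 0.28 | 0.26 (0.26) | 0.95 (0.97) |

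For SGRQ with two arms, the main effect has 0.07, 0.10 and 0.14, and group-by-time has 0.62, 0.49 and 0.62.

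The group-by-time test keeps its power but is not specific. A difference of 0.42 at 3 months alone, with nothing at 6 months, gives the same sum of squares (0.1176). It is therefore significant just as often: 0.95 with two arms, 0.97 with three. In the three-arm model, an effect in one programme only, the other being no better than standard care, also gives 0.97.

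**4. The 6-month contrast, one arm versus SC, baseline as covariate.** Residual SD √(1−0.85²) = 0.527. PIH: (0.42/0.527) × √(41/2) = 3.61, power 0.946. SGRQ: (0.27/0.527) × √(41/2) = 2.32, power 0.630. The variance relative to change scores is 0.2775/0.30 = 0.925, a reduction of 7.5%.

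**5. Sensitivity to ρ (PIH, two arms, no 3-month effect).**

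| ρ | Main effect | Group-by-time | 6-month ANCOVA |
|---|---|---|---|
| 0.85 | 0.10 | 0.95 | 0.95 |
| 0.70 | 0.11 | 0.71 | 0.75 |
| 0.50 | 0.12 | 0.48 | 0.58 |

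If 0.42 and 0.27 are instead in units of the SD of change, the two-sided change test has power 0.468 and 0.227.

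**The case against.** The strongest reply is that dilution is not built into a repeated-measures ANOVA. With a pre-randomisation visit in the model, the usual treatment test is group-by-time. The Sample Size section describes its effect size as one of change, which fits that reading. That term has PIH power 0.88 to 0.97, against 0.946 for the baseline-adjusted contrast. This stands, and it makes the power loss conditional on the main effect being used.

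A reader might infer that the main effect is the intended test, because the stated powers match it so closely. The protocol never says so, and a one-sided change-score test also comes close. A formula used for sizing would not settle which term is tested in any case.

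A reader might also assume a single three-arm model with a 4-df interaction. The protocol does not say that all arms enter one model. Pairwise ANOVAs against SC would identify the arm with a 2-df test, though still not the visit.

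The term, contrasts and covariates can be left to a statistical analysis plan, which was not available for this review. Silence on them is therefore not the point. The point is that the protocol fixes a method that does not correspond to the comparison it sizes.

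Finally, adjustment for baseline adds little precision over change scores. Setting it against unadjusted 6-month scores would give 0.85² = 72%, but the protocol proposes no such analysis, so that figure does not apply.

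**Conclusion.** The mismatch holds: baseline is an outcome level in a three-visit ANOVA, while the trial is posed and sized on each programme versus standard care at 6 months. Its cost depends on the term used. With the main effect, PIH power is about 0.10 to 0.26. With group-by-time, power is kept at 0.88 to 0.97, but a significant result does not show the visit or, with three arms in the model, the arm.

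The documents do not support saying that the planned analysis will usually miss a real effect, or that the power was computed for the main effect. They support saying that one permitted reading would do the former, and that the stated powers match the latter.

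The figures assume 41 per arm, ρ = 0.85, effects in score-SD units, compound symmetry and no dropout. Lower correlations or another standardiser reduce the power of the 6-month tests. This should be fixed, but it is not a fatal flaw.

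**What to change.** Name the primary analysis as the difference in mean PIH at 6 months, SM versus SC and RM versus SC, adjusted for baseline PIH. One suitable form is a mixed model with the 3- and 6-month scores as outcomes, baseline as covariate, and arm, visit and arm-by-visit terms. Report each adjusted difference with its 95% CI, and make the 3-month contrast secondary. The same model can serve SGRQ and the other continuous scores.

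Restate the power for that contrast, giving the standardiser of 0.42 and 0.27 and the sidedness of alpha. If both are score-SD differences and the test is two-sided at 0.05 per contrast, power is about 0.95 for PIH and 0.63 for SGRQ.

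The cost is wording in two sections. Baseline scores are already collected and no extra data are needed. The main gain is a test that answers the stated question; the gain in precision over change scores is small.
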